### Interim analyses {21b}

These are low-risk behavioural intervention studies and they were preceded by a pilot study which provided preliminary safety data [29]. Although unlikely, adverse events and clinically significant deterioration will be monitored, discussed and reported (see Sect. 22), following recommendations [61]. The lead statisticians will look for clinically significant deterioration on any outcome at the midpoint of the trials. Clinically significant deterioration will be determined through RCI analyses from baseline to the immediate post-treatment. If clinically significant deterioration is detected, a standardised procedure will follow (see Sect. 22).

### Plans to give access to the full protocol, participant level-data and statistical code {31c}

The study protocol and any de-identified database or statistical code required to support the protocol will be supplied on request.

## Oversight and monitoring

### Composition of the coordinating centre and trial steering committee {5d}

This research does not comprise a large multi-centre RCT, and therefore it is exempted of having a trial coordinating centre. However, the principal investigator (PI) of the project and co-PI play a critical role in coordinating and implementing both RCTs. They provide expertise in planning, conduct, monitoring, analysis and reporting, and convene weekly with the research team.

The project’s Steering Committee (SC) consists of one psychologist, one oncologist and one patient’s representative. SC will convene biannually (or more frequently if required) to oversee the conduct and progress of the trial, adherence to the protocol and the chronogram, participants’ safety and consideration of any new information.

### Composition of the data monitoring committee, its role and reporting structure {21a}

N/A: Given the existence of designated team members for data management, members who monitor data integrity (PI and co-PI) and a SC that oversees participants’ safety, a data monitoring committee will not be established.

### Adverse event reporting and harms {22}

Although unlikely, given the behavioural nature of the interventions and the preliminary data on safety [29], adverse events and clinically significant deterioration will be monitored, discussed and reported, following recommendations [61].

Adverse events and other unintended effects of the trials will be monitored by the therapists of each intervention group. Possible adverse events are as follows: clinically relevant increases in psychological distress, from heightened emotional reactions when confronting difficult thoughts or memories; relevant physical complaints/discomfort (e.g. headaches, muscle tension) from practising unfamiliar exercises, such as the body scan exercise; interpersonal conflict that is disruptive to the group functioning.

Participants will be encouraged to self-report deterioration since the start of the interventions and lead statisticians will look for clinically significant deterioration on any outcome at the midpoint of the trials (see Sect. 21b).

The occurrence of adverse events or clinically significant deterioration will be reported to the involved Ethics Committees and to the SC (see Sect. 5d), who will determine whether they are likely to be related to the intervention and may give recommendations to the PI for the early termination of the trials. The PI has the ultimate authority over early termination, but she will be guided by Linden and Schermuly-Haupt’s [62] stopping rule: if related adverse events or clinically significant deterioration are observed in 20% (approximate base-rate for adverse events in psychotherapies) of the intervention cohort by the trial midpoint, the study will be terminated.

Participants who experience treatment adverse effect or related clinically significant deterioration will be unblinded, removed from the study and provided with appropriate healthcare. As stated before (see Sect. 30), there are no provisions for any additional post-trial care or to provide compensation to those who suffer harm from trial participation.

All adverse events and clinically significant deterioration will also be reported in the trials’ scientific outputs.

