#### Support group intervention

This intervention (comparator) comprises 8 weekly 90 to 120-min sessions intended to be delivered by two licenced psychologists, in a face-to-face or online group format. Table 2 presents the BC-related content of the intervention, which will be discussed among participants in each session. The facilitators of this intervention will engage in a purely moderating role (e.g. facilitators should guarantee that all the participants have the chance to participate, and no one will use that time extensively; facilitators should also intervene if a participant states inaccurate information). As it is the case with the Mind programme group, participants with two missed sessions will be considered intervention non-completers, but they will be allowed to maintain their participation (and included in intention-to-treat analyses).

**Table 2 Tab2:** Session content for the support group intervention

Session 1	Participant self-introduction, group rules and discussion of expectations related to the intervention
Session 2	Emotional impact of BC diagnosis
Session 3	BC treatment side effects
Session 4	BC impact on family and caregivers
Session 5	Work-related and physical impact of BC (e.g. fatigue)
Session 6	Body image and sexuality after BC
Session 7	Self-care strategies
Session 8	Conclusion and final remarks

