#### Treatment as usual (waiting list)

The inactive control group (study 2) will receive the usual treatment for cancer patients in Portugal. In this country, the public healthcare system does not offer psychological counselling or psychotherapy as part of the regular care of women with BC. To gain access to this service, a referral from a physician is needed and not always granted due to lack of resources. At the end of this project, the intervention that proves to be most efficacious will be offered to the participants allocated to this condition.

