#### Analyses by aims

Aim 1: Determine the efficacy of the Mind programme compared to an active (i.e. support group) and/or inactive (i.e. treatment as usual group) control condition at post-intervention and at 6-month follow-up period.

The planned analysis for each outcome is a repeated-measures linear mixed model, including polynomial simple slopes to identify non-linear change over time. Within-group and contemporaneous between-group post hoc comparisons, using independent- or paired-samples *t*-tests (as appropriate), adjusted for multiple comparisons using the modified Bonferroni adjustment, will be performed. The efficacy of the intervention can be inferred through the evaluation of the simple slopes for each treatment condition, whereby the experimental condition demonstrates a significant improvement in QoL scores over time, and this improvement exceeds that of the control condition. The clinical significance of changes presented by each participant will be determined by computing the reliable change index (RCI) and considering mixed models of repeated measures (i.e. growth modelling analysis). In the former, we will calculate primary or secondary outcome RCI for each participant between pre- and post-intervention, as well as pre-intervention and 6 months. An RCI of ± 1.96 is considered statistically significant at *p* = 0.05, and the proportions of participants within each treatment condition who demonstrate significant improvement, decline and no change will be recorded. Fisher’s exact test will be used to examine for significant differences in the proportion of change between treatment allocations. Finally, we will perform correlation analysis between the raw RCI values and demographic variables separately for each treatment condition. This final analysis is used to examine potential predictors of individual change and the nature of that change.

Aim 2: Determine the cost-effectiveness of the Mind programme compared to an active (i.e. support group) and/or inactive (i.e. treatment as usual group) control condition at post-intervention and at 6-month follow-up period.

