### Strengths

First, the pilot study of the Mind programme supported its methodological implementation, and patient and therapist feedback were used to optimise the intervention. Second, the use of an active control group. Compared to the control group(s), participants allocated to the Mind programme are expected to show a higher degree of improvement in cancer-specific quality of life and depressive and anxiety symptoms. Improvements in these outcomes are expected to lead to a concomitant decrease in miRNAs expression and inflammatory biomarkers, as well as to increased cellular immunity (study 1 only). Also, improvements in primary and secondary outcomes are expected to lead to decreases in healthcare resources consumption and in economic costs associated with BC, in both studies. Third, the analysis of the potential mechanisms of change of the Mind programme is an important aspect of the current research. Changes in cancer-specific QoL in the experimental group are expected to be due to improvements in mindfulness, psychological flexibility and self-compassion, and to be maintained over the follow-up assessment, especially in participants that continue mindfulness and compassion practice (prescribed for between-session practice) post-intervention. It is also possible that each intervention will be distinctively beneficial or particularly efficacious for certain subgroups of patients (e.g. higher in psychological distress severity at baseline, younger). This kind of finding would provide important data for treatment customisation in BC. At last, findings from these RCTs will inform about appropriate methods of supporting women with BC who are undergoing radiotherapy, and potentially have important implications for the integration of psychosocial support to optimise service design, delivery and customisation in this population. Findings will also support future studies that may evaluate the Mind programme or other ACT and/or compassion-based interventions for people with cancer, and potentially highlight the clinical relevance of integrative interventions in oncology.

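### Study 2 names no adverse-event monitor for the treatment-as-usual arm, and neither study describes adverse-event monitoring after the sessions, so discrete adverse events are not ascertained alike against usual care and late ones may be missed

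*Protocol article*

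**What the plan says.** The protocol article, under Adverse event reporting and harms {22}, gives three routes by which harm can come to light.

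- **Therapist monitoring of adverse events:** "Adverse events and other unintended effects of the trials will be monitored by the therapists of each intervention group". No other adverse-event monitor is named.
- **Self-report of deterioration:** "Participants will be encouraged to self-report deterioration since the start of the interventions". No form, question, timing or end date is given.
- **Outcome-based deterioration:** "lead statisticians will look for clinically significant deterioration on any outcome at the midpoint of the trials". Interim analyses {21b} defines this check: "Clinically significant deterioration will be determined through RCI analyses from baseline to the immediate post-treatment". The aim 1 analysis extends the RCI: "we will calculate primary or secondary outcome RCI for each participant between pre- and post-intervention, as well as pre-intervention and 6 months". It counts decline within each condition and compares the proportions between allocations with Fisher's exact test.

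The harms section lists three kinds of possible event: heightened distress, physical complaints from unfamiliar exercises, and disruptive conflict within the group. It promises that all adverse events and clinically significant deterioration will appear in the trial publications. It also has the ethics committees and the steering committee judge whether they are related to the intervention.

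On the third arm of study 2, Treatment as usual (waiting list) says: "The inactive control group (study 2) will receive the usual treatment for cancer patients in Portugal". Mind and support each have two psychologists and 8 weekly sessions. Assessments are at baseline, post-treatment and 6 months.

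**The concern.** The only named adverse-event monitors are people whom TAU women never meet. If the plan is followed as written, events in Mind and support are seen by a professional each week, while events in TAU surface only if a woman volunteers them. These women are around the time of radiotherapy, when distress and physical complaints can occur in any arm. A concurrent background rate is what makes an adverse-event count interpretable and a relatedness judgement defensible. Without like-for-like collection, TAU cannot supply that rate, and the active arms could look harmful when they are not.

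The second gap is in time. No therapist contact is described once the sessions end, yet the Strengths section expects benefit to last "especially in participants that continue mindfulness and compassion practice (prescribed for between-session practice) post-intervention". The harms section names practising unfamiliar exercises as a source of physical complaints, so exposure may continue after the described observation has ended.

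**Working it through.** The plan gives no adverse-event rate or harm calculation, so there is no figure of its own to reproduce. The check has three steps.

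**1. Which route reaches which arm, and for what**

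| Route | Mind, support | TAU (study 2) | Discrete adverse events? | Period described |
|---|---|---|---|---|
| Therapist monitoring | yes | no therapist or session | yes | no window stated; therapist contact described only for the 8 sessions |
| Self-report | yes | unclear: TAU has no intervention start | worded as deterioration | open, no form |
| RCI on outcomes | yes | yes | no: change in scale scores | midpoint check to post-treatment; final analysis also to 6 months |

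Only the first route is aimed at discrete events, and it does not reach TAU. The RCI picks up part of the same ground, for example distress through HADS. It compares scores at fixed assessments and does not record an episode of headache or muscle tension between them.

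**2. Size of the uncovered group and period**

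Inputs: minimum N = 153 (Sample size {14}) and allocation 2:2:1 (Trial design {8}).

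- Mind and support: 153 × 2/5 = 61.2 each, about 61.
- TAU: 153 × 1/5 = 30.6, about 31, one fifth of study 2.
- Period with described therapist contact: 8 weeks. If the 6 months run from baseline, 8/26 = 31%. If they run from post-treatment, 8/34 = 24%. The article does not say which applies. The figures concern therapist contact only, not the other two routes.

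**3. What unequal capture could do**

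Assumptions, none from the document: the same true risk p in Mind and TAU, full capture in Mind, and a share c captured in TAU. Expected counts are 61 × p and 31 × p × c, rounded. The expected apparent difference is p − p × c. P-values are from Fisher's exact test on the rounded counts.

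| True risk p | TAU capture c | Mind | TAU | Apparent difference | Fisher p |
|---|---|---|---|---|---|
| 20% | 0% | 12/61 | 0/31 | 20 points | 0.007 |
| 20% | 25% | 12/61 | 2/31 | 15 points | 0.129 |
| 20% | 50% | 12/61 | 3/31 | 10 points | 0.37 |
| 20% | 100% | 12/61 | 6/31 | 0 | 1.0 |
| 10% | 0% | 6/61 | 0/31 | 10 points | 0.093 |
| 10% | 25% | 6/61 | 1/31 | 7.5 points | 0.416 |
| 10% | 50% | 6/61 | 2/31 | 5 points | 0.713 |
| 10% | 100% | 6/61 | 3/31 | 0 | 1.0 |

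Every apparent difference comes from capture alone. Only the extreme case (20% risk, no capture) falls below 0.05, but the bias in the reported rates is there at any capture below 100%. The same arithmetic applies to support against TAU.

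**The case against.** Several stronger readings are tempting, and the documents do not support them.

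- **That harm rates cannot be compared between arms.** Study 1 has no TAU arm. RCI decline is computed for each participant and tested between all allocations, TAU included. That is a planned harm comparison collected in the same way in every arm.
- **That collection stops after session 8.** No end date is stated. Self-report is open-ended and the RCI runs to 6 months. What can be said is that no therapist contact or adverse-event monitoring is described after the sessions.
- **That women who stop attending leave observation.** The retention section {18b} continues outcome collection after discontinuation. They leave the therapist's view but not the questionnaires. The 10 to 30% attrition in the sample-size section is not a session-dropout rate.
- **That Mind and support detect events differently.** The support section says "The facilitators of this intervention will engage in a purely moderating role", and the body scan is a Mind exercise. But both arms have two licensed psychologists for the same number and length of sessions. A moderating role describes how discussion is led, not whether events are noticed. Support sessions also deal with difficult material, such as the emotional impact of diagnosis.

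Two further objections carry weight. First, no between-arm test of adverse events is planned, and the harm threshold at midpoint concerns the intervention cohort. That is right, but the promised publication of all events will set the arms side by side, and relatedness will be judged with the same material. Second, the article condenses fuller approved protocols, which may hold forms and windows. That rules out criticism of missing detail. It does not remove the point, because the article states who monitors, and that choice leaves one arm out.

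**Conclusion.** The point holds in limited form and merits an amendment. In study 2 about 31 of 153 women have no named adverse-event monitor, so rates of discrete events in Mind or support against TAU are not ascertained alike. The possible spurious excess runs from zero to the full true risk, depending on how many TAU events surface by other means. It reaches 20 points under the assumed 20% risk with no capture, and 10 points with half captured. Both the risk and the capture shares are assumptions.

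In both studies, events after the sessions may be missed, because no monitoring is described for that period. Deterioration measured by RCI is unaffected in any arm, and Mind against support has the same type of monitor in both studies.

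**What to change.** Add one short block of adverse-event items, identical in every arm, to the post-treatment and 6-month LimeSurvey forms in both studies. It should cover the categories in the harms section without reference to any exercise, add an open question, and ask about the time since the previous questionnaire. Conflict within the group has no counterpart in TAU, so that category can be compared only between Mind and support.

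Name these items as the source for between-arm adverse-event reporting. Keep therapist observations as an additional source and report them separately.

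The cost is an amendment and a few questions on forms that all arms already receive with reminders. The forms become slightly longer. Women assessed before the amendment will lack the items, and for them adverse-event rates against TAU should not be interpreted.

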### Recruitment {15}

In study 1, women being treated for BC in the Radiotherapy Service of CHUC will be invited to participate. The point of recruitment will be at the beginning of radiotherapy treatment. The trial will be introduced to potential participants by their radiotherapy physician. A screening interview will be conducted with interested patients to assess eligibility and obtain written informed consent.

In study 2, the trial will be disseminated among the Portuguese population via press releases, social media platforms (e.g. postings with relevant groups and communities via Facebook and Instagram) and BC patients’ associations electronic distribution lists. Women with BC will register their interest by completing a form hosted on a secure online platform, which can be easily found in the project’s website. Alternatively, interested persons can contact research staff via email provided in the study advertisements. A screening interview, conducted by phone call, is later conducted to assess eligibility and obtain electronic informed consent.

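### The 20% limit that guides termination is the rate the protocol itself calls ordinary, and it is also applied to an RCI screen on any outcome with no stated midpoint comparison with control.

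*Protocol article*

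**What the plan says.** **The limit.** Adverse event reporting and harms {22} gives the criterion as "if related adverse events or clinically significant deterioration are observed in 20% (approximate base-rate for adverse events in psychotherapies) of the intervention cohort" and the consequence as "by the trial midpoint, the study will be terminated".

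**The screen.** Interim analyses {21b} states: "The lead statisticians will look for clinically significant deterioration on any outcome at the midpoint of the trials". It adds: "Clinically significant deterioration will be determined through RCI analyses from baseline to the immediate post-treatment". The RCI cut-off of ±1.96 is in Statistical methods {20a}, Aim 1. That section also plans to record the proportions improved, declined and unchanged in each arm and to compare them with Fisher's exact test. Neither {21b} nor {22} says that this by-arm comparison will be available at the midpoint.

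**The review and the decision.** Section {22} sends adverse events and deterioration to the Ethics Committees and the Steering Committee, "who will determine whether they are likely to be related to the intervention and may give recommendations to the PI for the early termination". On the decision itself it says: "The PI has the ultimate authority over early termination, but she will be guided by" the cited rule. The next paragraph reads: "Participants who experience treatment adverse effect or related clinically significant deterioration will be unblinded, removed from the study". Section {21a} states that no data monitoring committee will be set up.

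**The population.** For study 1, Recruitment {15} says: "The point of recruitment will be at the beginning of radiotherapy treatment".

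**The concern.** A safety limit should separate an unusual rate of harm from the background rate. Here three things blur that separation.

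1. The limit equals the background rate that the protocol itself quotes.
2. That background rate is for adverse events, but the limit also covers RCI declines. These are a different quantity, and their chance rate depends on how many scores are examined. The text does not fix that number.
3. No control-arm figure is stated for the midpoint. Women in study 1 enter as radiotherapy begins, so some scores may worsen for medical reasons. A count in one arm does not show whether the programme contributed.

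The wording adds two ambiguities. It is unclear whether *related* governs deterioration in the stopping count, and whether the rule guides the decision or settles it.

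At stake is the usefulness of the main numerical safeguard in both trials. Read literally, it could point towards stopping because of background variation. If it is set aside as too sensitive, the numerical limit adds little to the other monitoring.

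**Working it through.** **Inputs**
- Limit: 20% of the intervention cohort ({22}).
- Study 1: 75 women per arm ({14}). Half of that is 37.5, so 37 or 38 Mind women.
- Study 2: 153 women at 2:2:1 ({14}). The Mind arm is 153 × 2/5 = 61.2, about 61, and half of that is about 31.
- Attrition: 10-30% in study 1, up to 30% in study 2 ({14}).
- RCI cut-off: ±1.96 ({20a}).
- Assumptions: the intervention cohort is the Mind arm, and the midpoint lies somewhere between half and full enrolment. The article defines neither term.

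**The plan's own figures.** The 20% comes from a cited source, so there is nothing to re-derive. The RCI cut-off reproduces: 2 × (1 − Φ(1.96)) = 0.050, which is 0.025 in the declining direction.

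**Step 1: chance of reaching the limit at the quoted base rate.** The limit is reached at r = ⌈0.20 × n⌉ women. With X ~ Binomial(n, 0.20), P(X ≥ r) is:

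| Cohort | n | r | P(reach) |
|---|---|---|---|
| Study 1, full | 75 | 15 | 0.55 |
| Study 1, full, 30% attrition | 52 | 11 | 0.47 |
| Study 1, half | 38 | 8 | 0.50 |
| Study 1, half | 37 | 8 | 0.47 |
| Study 1, half, 10% attrition | 34 | 7 | 0.53 |
| Study 1, half, 30% attrition | 26 | 6 | 0.42 |
| Study 2, full | 61 | 13 | 0.45 |
| Study 2, full, 30% attrition | 42 | 9 | 0.47 |
| Study 2, half | 31 | 7 | 0.43 |
| Study 2, half, 30% attrition | 21 | 5 | 0.41 |

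The range is 0.41-0.55.

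**Step 2: how many scores could count.** At construct level there are about 6: cancer-specific QoL, anxiety, depression, psychological flexibility, self-compassion and health-related QoL. The QLQ-C30 alone has 5 + 1 + 3 + 5 + 1 = 15 scales or items ({18a}). Adding the four named QLQ-BR23 areas, two HADS subscales, CompACT, the SCS total, and the EQ-5D index with or without its visual analogue scale gives 24 or 25.

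**Step 3: women flagged by measurement error alone.** With no true change, each score shows a false decline in 2.5% of women. For k independent scores the chance of at least one is 1 − 0.975^k. For k = 9 this is 1 − 0.975^9 = 0.204, so about nine independent scores already give 20%. Correlated scores were simulated as equicorrelated normal variables (200,000 draws). The last column takes n = 38 and r = 8 and assumes that every flagged woman counts.

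| Scores | Women flagged, correlation 0.5 to 0 | P(reach) |
|---|---|---|
| 6 | 10-14% | 0.04-0.16 |
| 9 | 14-20% | 0.13-0.52 |
| 15 | 18-32% | 0.38-0.95 |
| 24 | 23-46% | 0.67-1.00 |

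**Step 4: the wording of {22}.** In the stopping sentence, *related* stands before adverse events and not before deterioration. The sentence on committee review covers both, and the next paragraph attaches *related* to deterioration. Separately, the investigator is said to be guided by the rule, while the rule says that the study will be terminated.

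**Step 5: effect of the relatedness review.** If only 10% of women count after review (an assumed value), P(reach) falls to 0.01-0.05 over the cohorts in Step 1.

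**The case against.** The strongest reply is that the rule does not count raw RCI declines. Section {21b} describes a screen. Section {22} then sends what it finds to committees that judge relatedness, and the Steering Committee includes an oncologist ({5d}) who can weigh the effects of radiotherapy. The investigator keeps the final decision. On that reading the filter works, and Step 5 shows how far it could lower the chance of reaching the limit. This largely stands. It disposes of the stronger inference a reader might draw, that any decline on any score counts and that a harmless programme should be expected to meet the limit. A programme with a 20% adverse event rate is an ordinary one, not a harmless one, and at that rate the result is close to a coin flip.

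Four further points stand in part.
- With about six construct scores, measurement error alone usually stays below the limit. Larger figures need subscales to be counted, and the article does not say whether they are.
- Higher rates can be produced by using the power calculation's correlation of 0.5 as a pre-post correlation for every instrument. That treats true individual change as noise and is an assumption, so the conclusion does not rest on it.
- The cohort is not defined. Section {6b} calls both Mind and support intervention groups. If 27 of 38 women had post-treatment data and the denominator stayed at 38 (an assumption), a 20% rate among those measured would reach 8 women with probability 0.16.
- A reader might infer that no deterioration signal would remain if the limit were overridden. Therapist monitoring and self-report in {22} remain, and {20a} already contains a by-arm RCI comparison.

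The reply does not explain why the limit equals the quoted background rate. Nor does it remove the two inconsistencies in the wording. An RCI carries no information on cause, and no by-arm midpoint figures are stated to help the committees judge relatedness.

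**Conclusion.** The concern holds in a limited form. The limit that guides termination equals the rate that the protocol calls ordinary. A programme with only that rate reaches it with probability 0.41-0.55, if the cohort is the Mind arm between half and full enrolment and every event counts against those assessed.

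Applying an adverse event rate to RCI deterioration is a separate mismatch. Under measurement error alone the flagged share runs from 10-14% with six scores to about 18-46% with 15 to 24, depending on correlation. It can approach or pass 20% without harm if subscales are counted and the relatedness review does not remove those women.

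The documents do not establish that stopping is automatic, or that deterioration counts without review. Section {22} can be read either way on both points, and that is part of the defect. This should be fixed. It is mainly a reconciliation of wording, with one useful addition to the midpoint report.

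**What to change.** The sponsor should reconcile, in {21b} and {22}:
- the 20% limit with its description as the usual base rate of adverse events, and with its use for RCI deterioration;
- the scope of *related* in the stopping sentence with the review sentence before it and the removal paragraph after it;
- the guiding role of the rule with the statement that the study will be terminated;
- the screen on any outcome with the count that enters the limit, including what the intervention cohort and the midpoint are.

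The midpoint report to the Steering Committee should show the proportion with RCI deterioration in each arm, the between-arm difference and the proportion expected by chance for the scores examined. It can use the by-arm RCI method already planned in {20a}. Its purpose is to inform the judgement of relatedness. No threshold, list of outcomes or replacement stopping rule is proposed here; those are for the sponsor and the committees.

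The cost is a revision of wording and one extra by-arm table at the midpoint.
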